| De-identified blood samples will be analysed and stored in NUH Tissue Repository. Recruitment and follow-up survey data will be collected electronically via NUHS REDCap. Only study team members with delegated rights will be able to access the data under the supervision of PI and Site-PI. All survey data will be collected electronically via FormSG. A copy of de-identified data will be stored in a secured server at NUH. |  |
|  |  |
| **SAMPLE SIZE AND STATISTICAL METHODS** |  |
| Determination of Sample Size |  |
| The prevalence rate of IGM in NUH is currently at 10 to 15 patients per year. Based on a stepped rule of thumb, a minimum sample size of 30 will provide at least 80% power to detect a medium standardised effect size of between 0.3 to 0.7 based on a randomised two-group comparison (Machin et al, 2021). Assuming a 20% attrition rate, the sample size required for this study is 36 patients. This will be rounded up to a sample size of 40 patients over a period of 36 months. |  |
| Statistical and Analytical Plans The primary outcome of 6-month clinical or radiological complete response will be compared between arms using Chi-square test. The effect estimate will be quantified in terms of difference in proportion as well as relative risk (RR) and their associated 95% confidence interval (CI). The secondary outcomes of time-to clinical or radiological response and time-to-relapse will be evaluated via the Kaplan-Meier method. The differences in survival curves will be compared using log rank test, with the effect estimate quantified in terms of hazard ratio and its 95% CI. The primary analysis of this trial will be based on Intention-to- Treat (ITT). A Per Protocol (PP) analysis will be performed on all patients who have completed 6 months of treatment regimen as a sensitivity analysis.  Chi square test will be used to evaluate the proportion of side effects and requirement for percutaneous or surgical intervention during treatment between arms. Modified Poisson regression will be used to identify clinical or biomarkers that are associated with treatment response and quantify the effect in terms of RR.  Patient reported outcomes will be reported via a survey on FormSG, conducted online. The questions will be adapted from SF36 V1 Singapore version and EORTC-BR23. Below are the domains to be compared:   - - General Health   - Physical Health   - Mental Health   - Body Image   - Sexual Image   - Breast Health |  |
| **ETHICAL CONSIDERATIONS** |  |

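### Section 11.1 claims at least 80% power from 30 patients for standardised effects of 0.3 to 0.7; at an assumed two-sided 5% level the power is about 12% to 46%, and 15% to 58% even with all 40 analysed

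*Protocol*

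**What the plan says.** Protocol Section 11.1 (Determination of Sample Size) rests on one sentence. It opens "Based on a stepped rule of thumb", says that "a minimum sample size of 30 will provide at least 80% power to detect a medium standardised effect size of between 0.3 to 0.7", and places this in a two-arm setting: "based on a randomised two-group comparison". The next sentence adds attrition: "Assuming a 20% attrition rate, the sample size required for this study is 36 patients". That figure is then rounded up to 40, to be recruited over 36 months at a site that sees 10 to 15 such patients a year. Section 5.1 splits the 40 into 20 per arm.

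The section gives no significance level, no sidedness and no response rates. Section 11.2 makes 6-month clinical or radiological complete response the primary outcome, tested by chi-square. The difference in proportions and the relative risk are to be reported with "their associated 95% confidence interval (CI"), and the primary analysis is by intention to treat.

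**The concern.** In a comparison of two independent groups, 15 per arm is far too few for 80% power at a medium standardised effect, and most clearly so at the lower end of the quoted band. This sentence is the only statistical justification for the sample size, and it stands in the document that the ethics board must approve (Section 12.2).

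The protocol also states a directional efficacy hypothesis in favour of methotrexate (Section 2.1) and plans significance tests of it (Section 11.2). Someone who trusts the 80% would take a non-significant result as fair evidence against a medium difference. With the true power, such a result would say little.

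Two lesser points sit beside this. Nothing ties the standardised effect to the binary primary outcome, and the step from 30 to 36 uses the wrong formula for attrition.

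**Working it through.** **Inputs.** Total of 30, power of at least 80%, standardised effect d from 0.3 to 0.7, 20% attrition and final size of 40 (all Section 11.1); 1:1 allocation (Section 5.1). *Assumption:* two-sided 5%, in line with the 95% intervals in Section 11.2. Other levels are tried below.

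**Trying to reproduce the 80%.** With n per arm, the normal approximation is power ≈ Φ(d√(n/2) − 1.96). For n = 15, √(15/2) = 2.739:

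- d = 0.3: Φ(0.822 − 1.96) = Φ(−1.138) = 12.7%
- d = 0.5: Φ(1.369 − 1.96) = Φ(−0.591) = 27.7%
- d = 0.7: Φ(1.917 − 1.96) = Φ(−0.043) = 48.3%

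The exact two-sample t-test (noncentral t) is slightly lower:

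| Per arm | d = 0.3 | d = 0.5 | d = 0.7 | d with 80% power |
|---|---|---|---|---|
| 15 (the stated 30) | 12.5% | 26.2% | 45.7% | 1.06 |
| 16 (40 less 20%) | 13.0% | 27.8% | 48.3% | 1.02 |
| 20 (all 40) | 15.2% | 33.8% | 57.8% | 0.91 |

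**Other readings, power at d = 0.3 and d = 0.7:**

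- 15 per arm, one-sided 5%: 20% and 59%
- 15 per arm, one-sided 10% (normal approximation): 32% and 74%
- 15 per arm, one-sided 20% (normal approximation): 49% and 86%
- 30 per arm, two-sided 5%: 21% and 76%
- 30 per arm, one-sided 5%: 31% and 85%
- Effect read as Cohen's h for two proportions, 15 per arm, two-sided 5%, assumed control response 50% to 80.7%: about 12% at h = 0.3 and 37% to 46% at h = 0.7

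None gives 80% across the band. With 15 per arm and d = 0.3, 80% power would need a one-sided level of 1 − Φ(0.822 − 0.842) = 0.51.

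**Numbers needed for 80%, two-sided 5%.** n per arm ≈ 2(1.96 + 0.842)²/d² = 15.7/d², which is 175, 63 and 33 at d = 0.3, 0.5 and 0.7. The t-test gives 176, 64 and 34.

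**Precision with the planned size.** Half-width of the 95% CI for a risk difference = 1.96√(2p(1 − p)/n). At an assumed p = 50% in both arms:

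- 20 per arm: 1.96 × √(0.5/20) = 1.96 × 0.158 = 31 points
- 16 per arm: 1.96 × √(0.5/16) = 1.96 × 0.177 = 35 points

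Since p(1 − p) is largest at 50%, the interval narrows at higher response rates.

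**Attrition.** The stated 36 equals 30 × 1.2. After a 20% loss it leaves 36 × 0.8 = 28.8, below the stated minimum of 30. The right step is 30/(1 − 0.20) = 37.5, so 38. The planned 40 leave 40 × 0.8 = 32.

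**The case against.** The best defence is that this is a pilot, sized by a published rule of thumb, and that the 80% may belong to the main trial that such a rule serves. The trial is indeed called a pilot (Sections 1.2, 5.1 and 8.5). But the sentence attaches the power to this sample of 30, and no later trial is mentioned. If another meaning was intended, the sentence still has to say so, and the sponsor should have that option.

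Four other objections stand in part or in full:

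- *The level is assumed.* True, so 12% to 46% is conditional on two-sided 5%. The conclusion is not, because no level or reading tried above gives 80% across the band.
- *The trial enrols 40 and is analysed by intention to treat.* True, so 15% to 58% matters as much as the figures for 30. A reader might infer that the trial would miss any effect in the band more often than not. That fails at d = 0.7 with all 40 analysed, where power is 58%.
- *A standardised effect need not be continuous.* True. A reader might infer that the claim concerns a continuous outcome, but the text does not say so. What can be said is that no response rates link the effect to the chi-square test.
- *The attrition slip changes nothing.* True. A reader might infer that the trial is too small for its own attrition allowance, but 32 exceeds 30.

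It is also tempting to compute the power of the primary test from the 80.7% and 94% in Section 1.2. Those are a good response to a steroid and disease improvement on methotrexate, from two separate reports. Neither is complete response at 6 months, so they cannot serve as design rates.

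**Conclusion.** The power statement in Section 11.1 is wrong. Where it promises at least 80%, the stated 30 patients give about 12% to 46% and the planned 40 give between 13% (d = 0.3, 32 evaluable) and 58% (d = 0.7, all 40 analysed). The exact figures rest on a two-sided 5% t-test with equal arms. The finding that 80% is not reached across the band does not depend on that level.

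The wrong attrition formula is a minor, separate slip with no effect on the planned size.

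A reader might go further and conclude that 40 is an unsuitable size or that every between-arm test must be relabelled exploratory. The document does not support either step. A size set by feasibility is defensible for a pilot: 10 to 15 patients a year over 36 months is 30 to 45 patients. Changing the status of the primary comparison goes beyond correcting a figure.

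**What to change.** In Section 11.1, replace the power sentence with a statement that:

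- 40 is a pilot size limited by feasibility;
- at two-sided 5% it gives power of about 13% to 58% for standardised effects of 0.3 to 0.7, depending on the effect and on whether 32 or 40 patients are analysed;
- the expected 95% CI half-width for the difference in 6-month response is about 31 points (20 per arm) to 35 points (16 per arm) at an assumed 50% response, and narrower at higher response rates;
- a non-significant result is not evidence of no difference.

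If the 80% was meant for a later main trial, say so explicitly and still give the figures for this trial. Correct the attrition-inflated number from 36 to 38 and leave 40 as it is.

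The change is to text only. The number enrolled and the planned analyses stay the same. The one downside is that the stated figure becomes less favourable.

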| This is a prospective pilot randomised trial to study the effectiveness of prednisolone versus methotrexate in achieving clinical or radiological complete response for women with IGM. The study will be conducted in NUH. This study evaluates the effectiveness of each drug in terms of clinical and/or radiological response, time to resolution as well as total number of flares over a period of one year follow-up. This study can potentially identify a more effective treatment with fewer side effects for women with IGM as well as personalize drug choices for patients who are at risk of frequent flares. |  |
| **HYPOTHESIS AND OBJECTIVES** |  |
| Hypothesis |  |
| The hypothesis is that methotrexate has a higher 6-month clinical or radiologically complete response with lesser side effects than prednisolone. The time to clinical or radiological response is shorter in the methotrexate arm compared to prednisolone arm. Relapse and time to first relapse is lower and longer in the methotrexate arm compared to prednisolone arm. |  |
| Primary Objectives |  |
| The primary objective is to evaluate the 1) Proportion of patients who achieved clinical or radiological complete response at 6 months 2) Time to clinical response and time to radiological response, and 3) Proportion of patients with relapse in one year within affected breast between each arm. |  |
| Secondary Objectives |  |
| The secondary objectives include evaluation of:   1. Side effects 2. Frequency of percutaneous or surgical intervention required 3. Potential biomarkers that may predict response to treatment: eg IL-6, CRP and neutrophil to lymphocyte ratio (NLR) 4. Patient reported outcome measures 5. Validate survey instrument for IGM patients |  |
| Potential Risks and benefits |  |
| End Points – Efficacy |  |
| Benefits expected for the patient are the total remission of IGM or reduced relapsed/flare of IGM. |  |
| End Points – Safety |  |

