| *Screening*  After patient is consented to the study, a baseline blood test (32mls, including pregnancy test, Hepatitis B test, Hepatitis C test, full blood count, liver function test and renal function test) and chest X-Ray will be conducted during the baseline visit to assess for eligibility prior to enrolment to the treatment phase. Additional research blood (14.5mls, 1 tablespoons) will be collected at this baseline visit for research purposes. Patient may be exempted from chest X-Ray and/or blood test if patient has done the same test within 30 days.  Baseline demographics and relevant clinical variables of patients will be collected. The following demographic and clinical variables will be collected: age of presentation, pre-menopausal or post-menopausal status, parity / breastfeeding status, concomitant rheumatic conditions, personal or family history of tuberculosis, smoking or alcohol intake, presenting complaint, unilateral or bilateral involvement, affected quadrant of the breast, duration of symptoms and previous antibiotics prescription for treatment of IGM.  Information on comorbidities will be evaluated to ensure suitability for both treatment arms prior to recruitment. Examples include drug allergies, plans for pregnancy, ongoing infection, previous history of cancer, previous tuberculosis, epilepsy, diabetes, hypertension, kidney, liver, cardiac problems, osteoporosis, glaucoma, peptic ulcers, previous side effects to either prednisolone or methotrexate.  If patient fulfilled all the eligibility criteria after screening assessment, she will be randomised to either of the treatment arm.  If patient did not meet the full eligibility criteria (eg. Pregnant, hepatitis carrier or abnormalities in renal or liver panels), she will not proceed to the treatment phase. The data collected and additional blood samples will be kept for analysis.  *Treatment Phase*  Patient will be scheduled to attend a clinical visit (T_0_) to either breast or rheumatology clinic if she meets all eligibility criteria for the initiation of treatment dose. There will be a window period of ± 7 days for this clinical visit. Patient is required to complete a pre-treatment quality of life online survey (approximately 10-15 minutes).  Patient will be scheduled for blood test (8mls, 0.5 tablespoons) and clinical visits to either breast or rheumatology clinic at the 1^st^ (T_1_), 2^nd^ (T_2_), 3^rd^ (T_3_) and 6^th^ (T_4_) month to assess their signs and symptoms, and drug compliance. There will be a window period of ± 14 days for each of these clinical visits. Additional research blood (14.5mls, 1 tablespoons) will be collected on the 1^st^ (T_1_) and 6^th^ (T_4_) months.  Patients are required to undergo a breast ultrasound to assess for their radiological response during the 3^rd^ (T_3_) clinical visit. A window period of ± 14 days will be applicable. The initial measurement of the breast lesion or mass will be recorded in three dimensions – i.e. anteroposterior, superior-inferior, mediolateral measurements. If complete clinical and radiological complete response has been achieved on the 3^rd^ (T_3_) visit, the doctor will discontinue the drug in a safe manner and no further breast ultrasounds will be required. If the patient’s symptoms or signs have not resolved by the 3^rd^ (T_3_) clinical visit, patient’s drug dosage will be assessed by the rheumatologist and treatment may be continued up to the 6^th^ (T_4_) month period and a repeat breast ultrasound will be required at the 6^th^ (T_4_) month. If symptoms have not resolved by the 6^th^ (T_4_) month of clinical visit, the patient’s drug dosage may be up-titrated or will be given an addition of a second therapy, i.e. combination therapy of steroid and methotrexate may be used. For clinical visits mention above, it will coincides with standard care visit.  During the clinical visits, Tingting Hu et al’s “M- score” will be adopted to grade the severity of the disease. M score is being calculated during clinical visits for IGM patients regardless of trial status for objective follow up. This is a common practice. For this study, the score will be administered by their attending healthcare professional (not limited to breast surgeons, investigators, or breast care nurses).  The M-score will be the sum of the following:  1) Mass score  2) Erythema score  3) Fistula score  4) Pain score  5) Quality-of-life (QoL) score  The scoring criteria were defined as follows:  1) Mass score: 0 for the absence of mass by palpation; 1 for mass ≤3 cm by palpation; 2 for mass >3 cm by palpation.  2) Erythema score: 0 and 2 for the absence and presence of erythema, respectively  3) Fistula: 0 and 2 for the absence and presence of fistula, respectively  4) Pain Score: 0 for Visual Analogue Score (VAS) 0-2; 1 for VAS 3-5; 2 for VAS 6-10  5) QoL score: 0 for absence of effects on QoL; 1 for mild effects on QoL, where the patient does not require medical assistant; 2 for serious effects on QoL, where the patient requires medical assistant  The total M-score ranges between 0 and 10 and serves as a quantitative and objective measurement of the severity of the symptoms.  The primary endpoint will be the clinical complete response (cCR) rate, which is defined as the proportion of patients who have an M-score of ≤ 1 at ≤1 years after treatment.  The secondary endpoints will be as follows:   - - The time to cCR, defined as the median time to cCR post randomisation.   - The treatment failure (TF) rate, defined as the proportion of patients with TF at 1 year post randomisation. The TF status will be defined as follows:     - If the patient has an M-score ≥6 before randomisation, TF is defined as the M-score remaining at ≥6 at 1 month post randomisation.     - If the patient has an M-score between 4 and 5 before randomisation, TF is defined as the M-score remaining at ≥4 and never being lower than 4.     - If the patient has an M-score <4 at baseline but never reaches cCR after randomisation, TF is defined as the M-score being >5 at the follow-up and remaining above 5 for one month. - Relapse rate, which is defined as the proportion of patients who have M-score >4 among the patients who achieved CR.   Throughout the course of the study, there are possible flares and relapse of the disease. Flares will be defined as any increase in M-score or lesion size on ultrasound whilst on therapy. While relapse will be defined as recurrence of symptoms or signs of IGM in the breast after previously experiencing complete resolution following therapy. If relapse occurs, patient will restart the same treatment arm for 6 months.  In the event of flares, blood test (8mls, 0.5 tablespoons) and additional research blood (14.5mls, 1 tablespoons) will be collected and the allocated treatment for the patient will be up-titrated by the doctor. In event of relapse, treatment for the patient will be reinitiated as per the allocated arm.  Additional research blood samples collected during the trial will be used for gene expressing profiling to identify unique patterns of gene expression that can be used to diagnose IGM and predict its treatment response.  Regardless of treatment arm, patient will be monitored by either breast surgeon or rheumatologist. Surgeons will assess for eligibility into trial, clinical reviews, and ultrasound breasts interpretation. Rheumatologists will be monitoring for drug side effects and titration if required. In event of failure of medical therapy, surgeons will have to intervene accordingly for aspiration or surgical drainage. In the event where patients require aspiration or surgical drainage during the study, methotrexate or prednisolone should be continued unless there is evidence of sepsis. The frequency of aspiration or surgical intervention will be recorded as events during the study.  Whenever the disease has been resolved during the study period, the balance medication and/or packaging will be retrieved to do medication accounting and checking for adherence to assigned treatment arm.  If side effects were to develop, doctors will evaluate the severity of the side effects and withdraw the patients from the trial if needed. |  |

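### The 6-month primary outcome accepts clinical or radiological complete response, so read literally a woman with persisting fistula or erythema can be a success on an undefined scan result that only some women will have

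*Protocol*

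**What the plan says.** The protocol describes response in several ways.

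- **Section 2.2, first primary objective:** "Proportion of patients who achieved clinical or radiological complete response at 6 months". The hypothesis in 2.1 also uses *or*.
- **Section 11.2:** "The primary outcome of 6-month clinical or radiological complete response will be compared between arms using Chi-square test". One outcome is named, with one test and one set of effect estimates.
- **Section 1.2(c), design rationale:** "This study evaluates the effectiveness of each drug in terms of clinical and/or radiological response, time to resolution".
- **Section 6.3, primary endpoint:** clinical complete response only, "defined as the proportion of patients who have an M-score of ≤ 1 at ≤1 years after treatment".
- **Section 6.3, month 3:** the rule for discontinuing the drug joins the components with *and*: "If complete clinical and radiological complete response has been achieved on the" month-3 visit.
- **Section 6.3, month 6:** if symptoms have not resolved, the patient's "drug dosage may be up-titrated or will be given an addition of a second therapy". The scan result is not mentioned.

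The M-score items that matter most here are "Erythema score: 0 and 2 for the absence and presence of erythema, respectively" and "Fistula: 0 and 2 for the absence and presence of fistula, respectively".

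On ultrasound, section 6.3 says that the lesion or mass is measured in three dimensions. It gives no threshold for radiological complete response. A scan is compulsory at month 3. Under 6.3 none is required after complete response on both components at month 3, and a repeat is required at month 6 if symptoms or signs have not resolved. Figure 1 marks the month-6 scan as discretionary. Section 8.5 states that the trial is open label.

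**The concern.** An outcome called complete response should not include women whom the same protocol classes as clinically unresolved. Taken literally, the *or* in 2.1, 2.2 and 11.2 allows this. A scan read as complete overrides a persisting fistula or persisting erythema, although 6.3 excludes such a woman from clinical complete response and makes her eligible for further treatment at that visit.

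The radiological component has two further weaknesses. It has no definition, so whoever reads the scan decides what is complete. It is also not collected evenly: the women for whom 6.3 requires a month-6 scan are those who had not resolved by month 3. Under *or*, a scan can turn a non-responder into a responder but never the reverse. With treatment known to patients and staff, and with Figure 1 leaving the scan to the doctor, the primary result could depend on who is scanned.

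**Working it through.** The plan gives no response rate for this outcome, so there is no stated figure to reproduce. The check has three parts.

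**1. Which M-scores can coexist with no palpable mass?** The items and scores come from section 6.3. With mass = 0, the remaining items are erythema (0 or 2), fistula (0 or 2), pain (0, 1 or 2) and quality of life (0, 1 or 2).

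- Possible patterns: 2 × 2 × 3 × 3 = 36, with a maximum total of 2 + 2 + 2 + 2 = 8.
- Patterns with total ≤1: all items zero, pain 1 alone, or quality of life 1 alone, which makes 3.
- Patterns that fail the clinical cut-off: 36 − 3 = 33.
- Of these, patterns with fistula, erythema or both: 36 − (3 × 3) = 27. Each totals at least 2.
- Patterns with total ≥6: with both signs present (4 points), pain plus quality of life must be at least 2, which gives 3 + 2 + 1 = 6. With exactly one sign present (2 points, two ways), pain plus quality of life must be 4, which gives 2 × 1 = 2. The total is 8.

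Pain differs from the two signs. Alone, it fails the cut-off only at VAS 6–10 (score 2). At VAS 3–5 it scores 1 and clinical complete response is met.

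If the scan were read as complete, all 33 failing patterns would count as success under 11.2.

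**2. Who can enter through the scan?**

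| Status at month 3 | Month-6 scan in 6.3 | Month-6 scan in Figure 1 |
|---|---|---|
| Clinical and radiological response both complete | Not required | Discretionary |
| Symptoms or signs not resolved | Required | Discretionary |

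The scan changes a woman's classification only if she is not a clinical responder at month 6. Such women come mainly from the second row.

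**3. What happens to the rates and the between-arm difference?** In each arm,

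P(either) = P(clinical) + P(scan only).

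The rate under *or* is therefore never below the clinical rate. For example, with assumed rates of 60% clinical and 50% radiological, it lies between 60% (every scan responder is also a clinical responder) and 100% (least possible overlap).

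The difference between arms changes by the difference in scan-only rates, which can have either sign. The protocol gives no radiological rates, so the rates below are assumptions, with the components taken as independent. Then P(scan only) = r × (1 − c), where c is the clinical and r the radiological rate.

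| Assumed rates, arm 1 v arm 2 | Scan only | Either | Clinical difference | *Or* difference |
|---|---|---|---|---|
| c 60% v 75%, r 50% v 65% | 20% v 16.25% | 80% v 91.25% | 15 points | 11.25 points |
| c 30% v 45%, r 20% v 35% | 14% v 19.25% | 44% v 64.25% | 15 points | 20.25 points |

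At the higher rates *or* narrows the difference. At the lower rates it widens it.

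**The case against.** **The *or* may list two outcomes.** Section 2.2 gives time to clinical response and time to radiological response as two quantities, and 11.2 restates them with *or*. Section 1.2(c) writes *and/or*. This stands in part: the text is not beyond doubt. For the binary outcome, however, 11.2 speaks of a single primary outcome with one test, which favours the composite reading.

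**A clear scan with an open fistula is hypothetical.** Radiological complete response is undefined, so it is an inference that such a woman would be read as complete. This stands, and it is why the definition belongs in the fix. Nothing in the protocol rules the case out.

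**A treatment rule is not an endpoint.** A stricter condition for stopping the drug at month 3 does not by itself contradict a looser outcome at month 6. This also stands. The contradiction is with 6.3's own primary endpoint, and the treatment rules are not judged here.

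**Inferences a reader might draw that the documents do not support.**

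- *The or costs power.* The direction depends on rates that the protocol does not give.
- *The outcome should require both components.* The women with the best month-3 response need no month-6 scan under 6.3, so they could not be scored.
- *A woman with M-score ≤1 and a residual lesion on ultrasound is misclassified.* She meets the protocol's own clinical definition.
- *33 of 36 is a frequency.* It counts score patterns and does not say how often they occur.

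**Conclusion.** The concern holds in a limited form. Sections 2.1, 2.2 and 11.2, read as one composite, let a radiological result alone make a complete responder, including a woman with fistula or erythema who cannot meet 6.3's cut-off. Section 6.3 names clinical complete response alone as primary, and radiological complete response is undefined. The month-6 scan is targeted in 6.3 and discretionary in Figure 1, so in an open-label trial the extra route to success is open mainly to women still symptomatic at month 3.

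The size cannot be given in patients. The documents support only that the *or* rate equals or exceeds the clinical rate, and that 33 of the 36 score patterns without a palpable mass could be reclassified. The conclusion rests on the composite reading of 11.2 and on such scans being read as complete.

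**What to change.** 1. In 2.1, 2.2 and 11.2, define the 6-month primary outcome as clinical complete response, M-score ≤1 at the month-6 visit. Bring the same phrase in 1.2(c) and 5.1 into line.
2. Reconcile this with the primary endpoint in 6.3, whose time frame is up to one year.
3. Define radiological complete response and report it as a separate secondary proportion, stating who was scanned at month 6. Reconcile 6.3 and Figure 1 on whether that scan is required.
4. Analyse time to clinical response and time to radiological response separately, as 2.2 lists them.
5. Do not require both components unless the month-6 scan schedule, or a stated carry-forward rule for women complete on both at month 3, makes every woman assessable.

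The cost is mainly wording, plus one new definition. The M-score is already part of the clinical visits, so no new assessment is needed. The downside is that the reported response rate will be equal to or lower than under *or*.

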| This is a prospective pilot randomised trial to study the effectiveness of prednisolone versus methotrexate in achieving clinical or radiological complete response for women with IGM. Patient will be recruited from NUH and written informed consent will be obtained prior to screening and enrolment. Patient will be randomised to one of the treatment arms.  The 2 arms consist of:   - Control arm (20 patients):   - Prednisolone tablet will start at 20mg daily for first 2 weeks (Refer to Figure 2 for tapering doses) with 20mg of omeprazole daily (Refer to Section 8.6) - Experimental arm (20 patients):   - Methotrexate tablet will start at 10mg once a week for the first month (Refer to Figure 2 for increasing of dosage) with 5mg of folic acid (Refer to Section 8.6) |  |
|  |  |
| **METHODS AND ASSESSMENTS** |  |
| Randomisation and Blinding |  |
| Permuted block randomisation will be performed with randomly varying block sizes of 4 and 6. Eligible and consented participants will then be randomly assigned to either of the treatment arm based on their baseline visit date. |  |
| Contraception and Pregnancy Testing |  |
| We do not accept women who self-report or test as pregnant during recruitment. |  |
| Study Visits and Procedures |  |
| **Study Visits and Procedures** |  |

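### The primary comparison is valid but leaves baseline M-score unused; recording it before randomisation and prespecifying an adjusted risk difference is a cheap improvement (low severity)

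*Protocol*

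**What the plan says.** - **Primary analysis (protocol 11.2).** "The primary outcome of 6-month clinical or radiological complete response will be compared between arms using Chi-square test". The effect is to be given as a difference in proportions and a relative risk with 95% confidence intervals. No covariate is named. Modified Poisson regression appears in the same section, but only to look for clinical factors or biomarkers associated with response, not to compare the arms.
- **Randomisation (6.1; arm sizes in 5.1).** "Permuted block randomisation will be performed with randomly varying block sizes of 4 and 6". No stratification factor is named, and each arm has 20 patients. Section 8.5 makes the trial open label.
- **Clinical response (6.3).** It is "defined as the proportion of patients who have an M-score of ≤ 1 at ≤1 years after treatment".
- **Baseline M-score (6.3).** The treatment-failure rule depends on it: "If the patient has an M-score ≥6 before randomisation, TF is defined as the M-score remaining at ≥6 at 1 month post randomisation". The section also says "M score is being calculated during clinical visits for IGM patients regardless of trial status for objective follow up", and Figure 1 marks a clinical visit at baseline. But the M-score has no row in Figure 1, is not among the listed baseline variables, and is described under the treatment phase.

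**The concern.** Starting severity is a natural candidate predictor of whether a patient ends at an M-score of 1 or below, because both are measured on the same scale. The trial needs the starting score anyway. In a 40-patient trial without stratification, the arms can differ noticeably in severity by chance. The planned analysis has no means of allowing for that, and an adjustment chosen after the imbalance is seen would be post hoc. If the score is prognostic, adjusting for it would also narrow the confidence interval at almost no cost.

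**Working it through.** The protocol gives no figure for the value of adjustment, so there is none to reproduce.

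**Inputs from the protocol.** 20 per arm (5.1); no stratification (6.1); clinical response at M-score ≤1 (6.3). The background cites complete response of up to 75% with methotrexate (1.1), a good response in 80.7% with a steroid, and improvement in 94% with methotrexate (1.2a). None of these is a design assumption.

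**Assumed, because the protocol is silent.** Two-sided 5% level; baseline scores spread over 2 to 10; odds of response changing 1- to 5-fold per SD of baseline M-score; and 50% vs 80% as a scenario with a large effect.

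**Step 1: how often the arms differ.** The between-arm difference in mean baseline score, in SD units, has standard deviation √(2/20) = 0.316. So P(|difference| > 0.5) = 2 × [1 − Φ(0.5/0.316)] = 2 × [1 − Φ(1.58)] ≈ 0.114. Simulation gives about 12%.

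**Step 2: what such an imbalance does.** Among randomisations beyond 0.5 SD, the mean absolute difference is 0.316 × φ(1.58)/[1 − Φ(1.58)] = 0.316 × 0.114/0.057 ≈ 0.63 SD. With 75% response in both arms, the slope of risk per SD is roughly ln(OR) × 0.75 × 0.25.

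- 1.5-fold: 0.405 × 0.1875 × 0.63 ≈ 5 percentage points in favour of the milder arm.
- 2-fold: 0.693 × 0.1875 × 0.63 ≈ 8 points.

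Simulation of the same setting gives 5, 8, 10 and 13 points at 1.5-, 2-, 2.7- and 4-fold. In those trials the adjusted estimate stays within 1 point of zero.

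**Step 3: validity over all randomisations.** With no true effect, chi-square rejects in 5.0-5.6% of simulated trials. The linear model with baseline M-score rejects in 5.1-5.5% (HC1 errors, t quantile). Both hold the level.

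**Step 4: precision.** With no association, adjustment costs a factor of about 1 + 1/(2×20 − 4) = 1 + 1/36 = 1.028 (normal covariate), an increase of about 3%. Simulated change in the variance of the risk difference, adjusted against unadjusted:

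| Odds of response per SD (assumed) | 75% in both arms, or 50% vs 80% | 80.7% vs 94% |
|---|---|---|
| no association | +2 to +3% | about +4% |
| 1.5-fold | 0 to +2% in one set of runs, −2% in another | about +1% |
| 2-fold | −5 to −6% | −1 to −2% |
| 2.7-fold | −11 to −12% | about −6% at 3-fold |
| 4-fold | −19 to −23% | about −9% |

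**Step 5: power at 50% vs 80%, 20 per arm.** Chi-square against the adjusted model, with leverage-corrected (HC2) errors and a t quantile on 40 − 3 = 37 degrees of freedom:

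- no association: 52% to 50%
- 1.5-fold: 53% to 53%
- 2-fold: 53% to 55%
- 3-fold: 53% to 58%
- 5-fold: 53% to 65%

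At 80.7% vs 94%, power is 22-24% unadjusted and 23-24% adjusted. Adjustment does not bring power to 80% in any scenario tried.

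**Step 6: the error variant matters at n = 40.** In null runs, HC0 with a normal quantile rejected 6-7.6%, which is too often. HC1 with a t quantile held near 5%. HC3 gave 4.2-4.5%. HC3's caution costs about 3 points of power at 1.5-fold (53% to 50%) and about 1 at 2-fold.

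**The case against.** The strongest reply is that nothing here is wrong. The test follows from the randomisation, no stratification factor is ignored, and chance imbalance is already counted in the 5% error rate. The imbalance figure in step 1 applies to any unstratified covariate with 20 per arm. All of this stands. A reader might infer that the chi-square result is biased or its error rate inflated; step 3 shows that it is not. Step 2 describes only the subset of randomisations that happen to be unbalanced.

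A reader might also infer that precision is definitely being lost. The protocol does not support that either. It gives no figure for how strongly baseline M-score predicts response, and with weak association the gain is nil or slightly negative. The link may be diluted further, because the primary outcome can also be met on ultrasound, and the M-score definition of clinical response in 6.3 is tied to one year rather than six months. With high response there is also little to model: 80.7% and 94% imply 20 × (1 − 0.8735) ≈ 2.5 non-responders per arm, against 5 per arm at 75%.

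Finally, supportive adjusted analyses are often left to a statistical analysis plan, which is not shown. That limits the severity but does not remove the point. The protocol itself names the primary analysis without the score, and its visit schedule does not secure that the score is recorded before allocation.

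**Conclusion.** This is a low-severity improvement, not an error. The planned comparison is valid but does not use a baseline measurement that the protocol's own treatment-failure rule requires. An imbalance above 0.5 SD has a probability of about 11-12% and would go uncorrected. If it occurred with no true effect and 75% response, it would shift the estimate by about 5 to 13 points for prognostic strengths of 1.5- to 4-fold. The variance gain is conditional: essentially none up to 1.5-fold odds per SD, 5-6% at 2-fold and 19-23% at 4-fold, and at most about 9% over that range if response is as high as 80.7% vs 94%. These figures rest on assumed prognostic strength, score distribution and response rates. That the score exists before randomisation is a reasonable inference from the treatment-failure rule, but the schedule does not state it.

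**What to change.** 1. Add M-score to the baseline variables in 6.3 and as a row in Figure 1, taken before randomisation. In an open-label trial, a score taken at T0, after allocation, would be a weaker covariate.
2. In 11.2, prespecify the risk difference adjusted for baseline M-score as one continuous covariate, from a linear model with small-sample robust errors: HC1 with a t quantile, or HC3. Name the variant.
3. Take the adjusted relative risk from modified Poisson regression, extending its stated use to the treatment comparison.
4. Report the unadjusted chi-square, risk difference and relative risk beside these, and state in advance which result leads.

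**Cost:** a line in the schedule, one or two sentences in 11.2, and trivial analysis work. If baseline M-score proves barely prognostic, the adjusted analysis gives up to about 2 points of power with HC1, or about 3-5 with HC3.
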